## Methods/Design

This is a three-arm randomized controlled trial that will examine outcomes at baseline, posttest (approximately 10 weeks post baseline), and 6 months. Ethical approval for this study was obtained by the University of Michigan Medical School Institutional Review Board and the Subcommittee on Human Studies in the Veteran's Affairs Ann Arbor Healthcare System. The overall goal of the study is to examine the effectiveness of a tailored activity pacing intervention for adults with symptomatic knee or hip OA. The primary outcomes are fatigue and pain.

The specific aims are:

Aim 1: To examine the effectiveness of a tailored activity pacing intervention on fatigue, pain, and physical function.

Aim 2: To determine if increased arthritis self-efficacy post intervention is related to improvements in symptom severity and function.

Aim 3: To evaluate the effect of tailored activity pacing on physical activity.

Eligible individuals are randomly stratified by age and gender into one of three arms: tailored activity pacing intervention, general activity pacing intervention, or usual care. The tailored and general activity pacing interventions are equivalent in session number and length. Participants are involved in study procedures over 6 months. For the intervention groups, involvement consists of 3 individual sessions, 3 testing visits, 3 home monitoring periods, 3 weekly follow-up phone calls, and monthly contact phone calls until the outcome assessment at 6 months. The usual care group participates in all activities described above except for the intervention sessions and the 3 weekly follow-up phone calls.

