Other secondary outcomes and potential moderators include physical function, assessed by the 6 Minute Walk Test [57], a commonly used, validated measure of physical performance in adults; arthritis self-efficacy, the perceived ability to manage arthritis and pain and fatigue symptoms, measured by the Arthritis Self Efficacy Scale [58]; and other variables such as knee extension strength (as measured by a hand-held dynamometer), and general health status variables (e.g., BMI, self-reported chronic conditions, depression using the Geriatric Depression Scale [59], medication use). In addition, PA will be assessed by a wrist-worn accelerometer [Actiwatch-Score, Phillips Respironics-Mini Mitter Co, Bend OR] that measures changes in acceleration. Although it is worn on the wrist, it is highly associated with whole-body movement [60,61]. Changes in acceleration are recorded as activity counts and saved every 15 seconds. Higher activity counts reflect participation in higher intensity activities [62,63]. PA from the accelerometer will be aggregated in different ways. We will look at average activity counts and total activity counts that occur: 1) in the time between symptom reporting periods, 2) over each day, and 3) over the entire home monitoring period similar to our previous studies [40,41,64].

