### Data Analysis

The target sample size in this study is 156 participants. In our recruitment plans, we have factored in a 30% attrition rate to achieve this number. Although there are three arms to the study: tailored activity pacing, general activity pacing, and usual care group, the study was powered to find effects between the two active intervention groups (tailored activity pacing and general activity pacing). Specifically, the power analysis was based on our pilot data in which we compared the tailored activity pacing intervention with the general activity pacing intervention and detected large group differences using the effect size Cohen's d [65] on BFI fatigue severity and interference (d = .79 and 1.1 respectively) at 10 week-follow-up. Based on a 2 group t-test at a significance level of p = .05, we will have greater than 90% power to detect an effect size of .74 or larger with 40 people in each of the two active intervention groups. Because most people with OA do not receive this type of intervention, it is important to compare the active intervention groups to a group receiving usual care. The study was powered to detect treatment effects between the active intervention groups; therefore we will also have sufficient power to detect differences between the active intervention groups and usual care group.

To examine the effectiveness of a tailored activity pacing intervention on fatigue, pain, and physical function, we will use repeated measures analysis of variance (RM ANOVA) models to analyze the responses (pain, fatigue, and 6 minute walk test) at baseline, 10 weeks, and 6 months for the three treatment groups (tailored activity pacing, general activity pacing, and usual care group). This will allow us to estimate the effects of treatment group, time point and the treatment × time interaction. Similarly, we will use RM ANOVA models to determine if increased arthritis self-efficacy post intervention is related to improvements in symptom severity and function and to evaluate the effect of tailored activity pacing on physical activity.

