## Discussion

Although non-pharmacological treatment is recommended for people with knee and hip OA to manage symptoms, much of the evidence-base has examined these strategies in the context of a program of skills rather than individually. This study is examining the effect of a brief, individually-tailored, OT-led activity pacing intervention on pain and fatigue in adults with knee and hip OA. Given the positive effects of the tailored activity pacing approach compared to general activity pacing on fatigue in a small pilot study, we hypothesize that fatigue in particular will be improved with the tailored activity pacing intervention. We will also explore arthritis self-efficacy as a potential mechanism of change and the effects of pacing on PA at the 6 month follow-up period in an exploratory analysis.

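### Aim 2 asks whether gains in self-efficacy relate to improvement, but the repeated-measures ANOVA described for it has only arm and time effects and no self-efficacy term

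*Protocol article*

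**What the plan says.** The Methods/Design section of the protocol article lists the aim as "Aim 2: To determine if increased arthritis self-efficacy post intervention is related to improvements in symptom severity and function".

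Data Analysis first sets out the Aim 1 models, which are repeated-measures ANOVAs "to analyze the responses (pain, fatigue, and 6 minute walk test) at baseline, 10 weeks, and 6 months for the three treatment groups". It says what they deliver: "This will allow us to estimate the effects of treatment group, time point and the treatment × time interaction". The next sentence, linked to these models by the opening word Similarly, turns to Aim 2: "we will use RM ANOVA models to determine if increased arthritis self-efficacy post intervention is related to improvements in symptom severity and function". The same sentence gives Aim 3, the effect of tailored pacing on physical activity, the same method. No further term is named for Aim 2.

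The Measures section places self-efficacy in a mixed list that opens "Other secondary outcomes and potential moderators include physical function". The Discussion says "We will also explore arthritis self-efficacy as a potential mechanism of change" and describes this work as exploratory.

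**The concern.** Aim 2 concerns the relation between two measurements that both change after randomisation. The effects described for the assigned model concern differences between arms over time. If self-efficacy is analysed that way, the result shows whether the arms differ in self-efficacy. If symptoms are analysed that way, it shows whether the arms differ in symptoms. Neither result shows whether participants who gained more self-efficacy also improved more.

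One of three stated aims could therefore go unanswered by its named analysis. There is also a risk in interpretation: if both measures improve in the tailored arm, a reader may take that as evidence of a mechanism, although it would occur equally if the two changes were unrelated within every arm.

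**Working it through.** **The plan's own figure.** The only power statement, in Data Analysis, is more than 90% for a two-group t-test at .05 with effect size .74 and 40 per active arm. Taken as two-sided (the article does not say), it reproduces: 0.905 with the noncentral t and 0.911 with the normal approximation. It concerns tailored against general pacing. No figure is given for Aim 2.

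**Question against model.**

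- Aim 1 asks whether arm alters the course of fatigue, pain and function. The arm-by-time term answers it.
- Aim 3 asks whether tailored pacing alters physical activity. The arm-by-time term answers it.
- Aim 2 asks whether change in self-efficacy is related to change in symptoms and function. It needs a coefficient for self-efficacy change, and none is described.

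Let Y be a participant's change in symptoms and M the change in self-efficacy. With one change score per participant, the arm-by-time test is a one-way ANOVA on change:

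Y = α(arm) + error.

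Aim 2 needs β in

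Y = α(arm) + βM + error.

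The first model does not contain M. Any pattern of arm means is compatible with any β within arms.

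**Illustration.** The 40 per arm comes from the power statement and is applied here to all three arms. Everything else is assumed: changes standardised to SD 1 within arm; M = m(arm) + e1; Y = y(arm) + β(M − m(arm)) + √(1 − β²)·e2; arm effects either none, or 0/0.4/0.8 SD on M and 0/−0.4/−0.8 SD on Y; 2,000 runs; tests at 5%. Each arm-by-time entry is the share of runs that rejected.

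| True β | Arm effects | Arm-by-time, self-efficacy | Arm-by-time, symptoms | Slope without arm (rejects) | Slope with arm (rejects) |
|---|---|---|---|---|---|
| 0 | none | 4.3% | 5.4% | 0.00 (5.2%) | 0.00 (5.2%) |
| −0.40 | none | 4.2% | 4.6% | −0.40 (99.4%) | −0.40 (99.4%) |
| 0 | present | 89.6% | 89.1% | −0.10 (17.9%) | 0.00 (5.2%) |
| −0.40 | present | 89.7% | 90.0% | −0.46 (100.0%) | −0.40 (99.6%) |

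The arm-by-time columns follow the arm effects and do not respond to β. They stay near 5% whether or not the association exists when arms do not differ, and near 90% whether or not it exists when they do. The slope with arm in the model recovers β in all four rows.

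The third row's slope without arm can be checked by hand. The between-arm variance is (0.16 + 0 + 0.16)/3 = 0.107, so the expected slope is −0.107/(1 + 0.107) = −0.096, which agrees with the simulation. In that row, a median split on self-efficacy change, entered as a factor without arm, rejected in 15.4% of runs.

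**The case against.** The strongest reply is that the linking word in the Aim 2 sentence may mean only the same family of models. A repeated-measures ANOVA with self-efficacy change as a covariate or factor, and its interaction with time, would estimate the association. A condensed article may leave such terms to the full plan. This stands against any claim that repeated-measures ANOVA as such cannot answer Aim 2. It does not remove the point, because the article names a method, describes its effects, and describes none involving self-efficacy. As written, the method does not match the aim.

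Some stronger readings are tempting, and the article does not support them:

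- **The answer will be confounded by arm.** This happens only if a self-efficacy term is fitted with arm left out, or if parallel improvement is read as a link. The article proposes neither.
- **Aim 2 requires a within-person association.** The article does not use that term. An association between participants' changes is a fair reading.
- **The false association can be sized from the article.** With two equal arms both shifted by d, and no correlation within arms, the pooled correlation is d²/(4 + d²): 0.5476/4.5476 = .12 at d = .74 and 1.21/5.21 = .23 at d = 1.1. But .74 is the detectable effect in the power statement and 1.1 is the pilot effect on fatigue interference. No self-efficacy effect is given, so this range is hypothetical.
- **Self-efficacy is called a moderator in one place and a mediator in another.** The Measures list mixes outcomes and moderators without assigning roles, and it includes the walk test, which is plainly an outcome. Baseline self-efficacy could also be a moderator while its change is a mediator. The wording deserves clarifying, but it is not a firm contradiction.

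It also stands that the Discussion already calls the mechanism work exploratory, which limits the consequences.

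**Conclusion.** The concern holds for the model as described. Followed literally, the Aim 2 analysis would test arm differences over time and leave the stated association unestimated. This is a mismatch between aim and named method, which goes beyond a detail left to a later document. It should be corrected before analysis.

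Its reach is limited. Aim 2 is not a primary comparison, and the fatigue and pain conclusions do not depend on it. The size of any wrong inference cannot be taken from the article. The simulated rates rest on assumed arm effects and an assumed slope, with one change score per participant in place of three visits. They show which quantities each analysis responds to, and do not forecast this trial's results.

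**What to change.** For Aim 2, replace the arm-by-time ANOVA with a regression or mixed model of the symptom or function outcome on baseline-to-10-week change in arthritis self-efficacy. Keep treatment arm in the model, and adjust for the baseline value of the outcome and for baseline self-efficacy.

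If the outcome is taken at 6 months, add a sensitivity analysis that also adjusts for the 10-week symptom level. Early symptom relief could itself raise self-efficacy and persist, so measuring self-efficacy earlier does not by itself establish the direction of the relation.

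Report the result as an exploratory association or mechanism analysis, in line with the Discussion. State that change in self-efficacy is treated as a candidate mediator. Baseline self-efficacy may remain a potential moderator. Say explicitly that improvement of both measures in the same arm will not be taken as evidence of a link.

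The cost is analysis wording and a little extra analysis. Outcomes are already examined at baseline, 10 weeks and 6 months. I assume the self-efficacy scale is given at the first two of these, as the aim's reference to a post-intervention increase implies, so no new data collection should be needed.

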## Discussion

Although non-pharmacological treatment is recommended for people with knee and hip OA to manage symptoms, much of the evidence-base has examined these strategies in the context of a program of skills rather than individually. This study is examining the effect of a brief, individually-tailored, OT-led activity pacing intervention on pain and fatigue in adults with knee and hip OA. Given the positive effects of the tailored activity pacing approach compared to general activity pacing on fatigue in a small pilot study, we hypothesize that fatigue in particular will be improved with the tailored activity pacing intervention. We will also explore arthritis self-efficacy as a potential mechanism of change and the effects of pacing on PA at the 6 month follow-up period in an exploratory analysis.
